
### Participant timeline {13}

The study protocol follows the SPIRIT 2025 statement recommendations (Fig. 1). See Fig. 2 for the pathway for each arm.

**Fig. 1 Fig1:**
[figure not shown]
SPIRIT timeline diagram

**Fig. 2 Fig2:**
[figure not shown]
Casting Away Trauma participant pathway

### Sample size {14}

#### Power analysis

Our main dependent variable will be PTSD symptoms (as measured using the PCL-5). The results from our developmental phase showed a significant group × time interaction for PCL-5 scores, with significant improvements at 2-week and 4-week post-intervention for the angling but not the control group. Given that the purpose of the NIHR call is to build robust evidence for the clinical impact of NBIs, it is imperative that study power should be based on the main DV of interest with the lowest difference scores (i.e. a difference score that will allow the power calculation of a sample large enough to detect a significant effect (should there be one). This is the effect size observed between groups at 4-week post-intervention in the developmental phase (Cohen’s d = −0.52). For a 2-tailed test with 95% power, an alpha of 0.05, and *d* = −0.52 effect size, the power analysis provides a sample size of *n* = 196 (98 participants in each group).

#### Recruitment sample size

The attrition rate after randomisation in the development phase was approximately 25%. We aim to randomise our power analysis sample size + 30% for the main phase. Thus, we aim to randomise 196 + 30% = 254.8 participants (rounded to 264: 132 intervention, 132 controls to facilitate 12 participants per intervention). By rounding to 264, we can ensure slots are filled across 22 scheduled sessions of 12 participants each. We have designed an RCT with 11 active intervention groups and 11 waitlist control interventions to be delivered after RCT data are collected. We will run eight angling interventions (four active and four controls) sequentially (a maximum of *n* = 12 participants in each session) in years 1 and 2 and six interventions (three active and three controls) in year 3.

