### Trial design {8}

A randomised waitlist-controlled superiority trial with an allocation ratio of 1:1 and a 4-week follow-up. The primary outcome will be assessed at 2-week and 4-week post-intervention and compared with the waitlist control group. The total follow-up period is 12 months (intervention group only).

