### Intervention description {11a}

The intervention is named *Casting Away Trauma* (CAT). Following our preliminary work and the developmental phase of the current project, we have a well-established and manualised protocol for the intervention:Day 1 am — Arrival at fishing lake, introduced to personal angling coach, shown to designated lakeside “swim” with tent and seat, health and safety briefing, set-up equipment, and recording of “arrival” process measuresDay 1 pm — Fishing instruction, fishing and social interaction, evening meal, and participants fish through the night or sleep as they chooseDay 2 am — Breakfast, fishing, and social interactionDay 2 pm — Fishing and pack-up equipment, recording of “departure” process measures, instructions on how to keep in contact via social media, etc.

Prior to their intervention, participants will be sent a letter and an infographic developed for the study visualising what to expect at the intervention. The venue will be available exclusively to participants. Professional angling coaches with Angling Trust certification will be provided at a ratio of 1:2 participants. As recommended by Husk et al. [7], participants will be supported to travel to the venue. iCARP’s “Lifted Lakes” venue has a covered socialising area with a fire pit, and participants are encouraged to bring warm clothing, since socialising with peers is a key component of the intervention. Participants are free to move around the lake and talk to other participants and use the communal area for socialising and taking warm drink breaks. Food will be cooked and shared by iCARP volunteers. At the end of the experience, participants will be encouraged to join a “Facebook” group in order to keep in contact via social media and will be offered a selection of exit routes. During this period, the wait group receives no intervention and continue with their normal day-to-day activities and usually care.

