## Statistical methods

### Statistical methods for primary and secondary outcomes {20a}

#### Primary outcome analyses

The key analysis relates to the comparison of pre- (2 weeks before the intervention) and post-intervention measures for the intervention and control groups taken at 2 and 4 weeks after the intervention). A mixed MANOVA with one between-group factor (intervention vs. waitlist control) and repeated measures on all outcomes (baseline vs. 4-week post-intervention) will be conducted.

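### The active arm is treated in 11 peer-group sessions, but the power calculation and the primary model assume independent participants; if outcomes correlate within session, precision and power are overstated

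*Protocol article*

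**What the plan says.** Under Recruitment sample size the Protocol article states: "We have designed an RCT with 11 active intervention groups and 11 waitlist control interventions to be delivered after RCT data are collected". Each session holds at most 12 people. Intervention description {11a} asks participants to bring warm clothing, "since socialising with peers is a key component of the intervention", and describes shared meals and a communal area. The same section says that the waitlist group receives no intervention during this period.

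The Power analysis paragraph sets its terms as follows: "For a 2-tailed test with 95% power, an alpha of 0.05", with d = −0.52. On the source of that d it says: "This is the effect size observed between groups at 4-week post-intervention in the developmental phase". The result is 196, or "98 participants in each group". The 30% added afterwards is tied to attrition, and the rounding to 264 serves to fill sessions.

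Primary outcome analyses names the model: "A mixed MANOVA with one between-group factor (intervention vs. waitlist control", with repeated measures on the outcomes. Secondary analyses reuses this structure for subgroups and secondary outcomes. The article does not mention session, clustering, an ICC or a design effect.

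**The concern.** People who spend two days and a night together share a peer group, meals, weather and on-site staff. The article itself treats peer support as a hypothesised active element and devotes eleven items to it. If peers affect one another's recovery, outcomes within a session will be more alike than outcomes across sessions, and 99 treated completers carry less information than 99 independent people. Individual randomisation does not remove a correlation that arises after allocation. Controls have no such grouping before their 4-week outcome, so the extra variance falls in one arm only.

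At stake are the width of the interval around the main treatment contrast and the 95% power claimed for a trial described as definitive. Only 11 sessions inform how far the treated mean varies from session to session.

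**Working it through.** **Inputs from the Protocol article.** Two-sided alpha 0.05, power 95%, d = 0.52 in absolute value, 98 per arm (Power analysis); 1:1 allocation (Trial design {8}); 264 randomised, 11 active sessions of 12, and "The attrition rate after randomisation in the development phase was approximately 25"% (Recruitment sample size).

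**Assumed.** ICC from 0.01 to 0.10, because the article gives none; total SD of 1 in both arms; equal session sizes; every active completer attended a session.

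**Step 1: reproduce the plan's figure.** The normal approximation gives n = 2(1.960 + 1.645)² / 0.52² = 96.1, so 97 per arm. The exact noncentral-t calculation gives 98 per arm, 196 in total, with power 95.2%. The stated figure is reproduced with a design effect of 1, so it holds no hidden allowance for clustering.

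**Step 2: spare sample.** 196 × 1.30 = 254.8, rounded to 264. After 25% attrition, 264 × 0.75 = 198, which is 99 per arm and 99 / 11 = 9 per active session. That is 198 − 196 = 2 above the requirement.

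**Step 3: partially nested variance.** With clustering in the active arm only:
- DE = 1 + (9 − 1) × ICC
- Var = DE/99 + 1/99
- true SE / naive SE = √[(DE + 1)/2]
- Satterthwaite df = (DE + 1)² / (DE²/10 + 1/98)

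Example, ICC 0.05: DE = 1.40; SE ratio = √1.20 = 1.095; naive SE = √(2/99) = 0.142, true SE = 0.156; 0.52/0.156 = 3.34; normal-approximation power = Φ(3.34 − 1.96) = 91.6%. Then df = 5.76 / (0.196 + 0.0102) = 27.9, and power from the noncentral t is 89.7%.

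| Assumed ICC | DE | True SE / naive SE | Power, normal | df | Power, small-sample t |
|---|---|---|---|---|---|
| 0 | 1.00 | 1.00 | 95.5% | 36.3 | 94.5% |
| 0.01 | 1.08 | 1.02 | 94.8% | 34.1 | 93.6% |
| 0.02 | 1.16 | 1.04 | 94.1% | 32.2 | 92.7% |
| 0.05 | 1.40 | 1.10 | 91.6% | 27.9 | 89.7% |
| 0.10 | 1.80 | 1.18 | 87.1% | 23.5 | 84.2% |

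The ICC 0 row shows that about one point of the loss in the last column is the price of few degrees of freedom, not of correlation. Power drops below 90% at an ICC of about 0.05 (small-sample t) or 0.07 (normal).

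**Step 4: rejection rate of an analysis that ignores session.** 2[1 − Φ(1.96 / SE ratio)] gives 5.9%, 7.4% and 9.8% at ICC 0.02, 0.05 and 0.10. This requires a zero average effect together with real variation between sessions.

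**Step 5: sensitivity.** With no attrition (132 per arm, 12 per session) and ICC 0.05, DE = 1 + 11 × 0.05 = 1.55. Power is then 96.3% (normal) or 95.0% (small-sample t), but the true SE is still 13% larger than the naive one. Applying the design effect to both arms would give 87.1% at ICC 0.05. That overstates the loss, since controls are not grouped in the randomised period.

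All figures are for the two-group comparison of PCL-5 on which the article bases its power. The joint MANOVA test was not computed.

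**The case against.** **The ICC is unknown.** This stands. A reader might infer that the standard errors are certainly too small and that 95% power is certainly missed. The article has no ICC and no session-level data, so the conclusion is conditional, and at ICC 0.01 to 0.02 it is minor.

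**Type I error.** A reader might infer that the primary test breaches its 5% level in general and tilts p-values towards the intervention. Neither follows. If the intervention does nothing for anyone, attending a session creates no correlation, recruitment-period effects should fall on both arms, and the naive test stays near 5%. The rates in step 4 need sessions that truly differ yet average to zero. Even then, understated variance produces excess rejections in both directions and does not bias the estimate.

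**It belongs to the analysis plan.** The section on non-adherence and missing data promises a detailed plan before data entry ends and leaves maximum likelihood open. The choice of degrees of freedom or residual structure can indeed wait for that. But this article already names a model with one between-group factor and states a power figure, and both rest on independence.

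**Exposure is less shared than it looks.** Coaches work at one to two participants, so a coach is not common to a whole session. Under intention-to-treat, non-attenders who return data are not clustered, which lowers the design effect. Both points stand. The peer-interaction argument does not depend on them.

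**Enlarging the trial.** A reader might infer that 264 is too few. With no ICC in the article there is no basis for a new number, and power stays at about 84% or more across the assumed range.

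**Conclusion.** The point holds in conditional form. The design is partially nested by the article's own description, and neither the sample size nor the named primary model allows for it. For any positive within-session correlation the naive standard error is too small. Over the assumed ICC range of 0.02 to 0.10 the understatement is modest to material, and power analysed with session taken into account runs from slightly to clearly below the stated 95%. The size rests on the assumed ICC, on 25% attrition spread evenly over sessions, and on all active completers having attended. The design remains usable; what needs correcting is the analysis and the power statement.

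**What to change.** 1. Carry a session code, keyed by participant ID, into the anonymous analysis file. Strategies to improve adherence {11c} describes only a log of arrivals, and Data management {19} does not say that session reaches that file, so the link has to be created.
2. Analyse PCL-5 with a method that accounts for session in the active arm. One example is a partially nested mixed model with a session effect in the active arm, controls as singletons, and small-sample degrees of freedom. Other methods that respect the grouping are defensible.
3. In Power analysis, state that 98 per arm assumes independence, and give power at the existing 264 over a range of ICC, for example 0.02 to 0.10.

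The cost is some wording in the article and the analysis plan, plus one variable in the data file. Recruitment is still open according to Trial status, so this can be settled before analysis. The downsides are somewhat wider intervals, a less favourable power figure, and a session variance that 11 sessions estimate imprecisely and may put at zero.

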### Recruitment {15}

Recruitment into the study will be via on online Qualtrics link embedded in the project website and on all recruitment materials. Potential participants can either engage via the project’s webpage or contact the study team via email or telephone. Participants complete a registration form via a Qualtrics platform in which demographic and PTSD severity (via PCL-5 items) information are requested via questionnaire items for purposes of randomisation. Alternative arrangements, such as paper copies of questionnaires, will be provided where requested by participants to ensure inclusivity; participants will be made aware of such options within recruitment materials and communications. Anonymity will be ensured whatever the media used. The website link permits self-referral, enabling us to reach those suffering from PTSD who are not receiving support from either NHS or charitable organisations.

#### Routes to promote direct self-registration

The development phase showed that the majority of participants were recruited via social media platforms including Facebook. We will advertise the study via the social media platforms (Facebook, Twitter, and Instagram) of organisations currently sponsoring iCARP work (angling companies Korda and Nash, which combined have over 527,000 followers on Facebook and 504,000 on Instagram). We will employ three Facebook “pushes” as we did in the development phase to specifically target military veterans and ESPs with particular attention to targeting minorities and women.

#### Routes to promote self-registration via referring agencies

We will provide stakeholders with capacity to refer/inform potential participants to access the online registration with a flier and information pamphlet that describes what the intervention has to offer as an extension to their existing provision. Feedback will be sought on draughts of the pamphlet from stakeholders, service providers, and our PPI. All recruitment materials are designed to convey inclusivity across gender, ethnicity, and religion via considered inclusion of diversity in imagery and messaging.

Stakeholders have been identified broadly as charities representing veterans and ESPs, Occupational Health Departments of ESPs, ESP outreach events and organisations, and social prescribers.

## Assignment of interventions: allocation

### Sequence generation {16a}

Participants will be allocated to the control or waitlist condition by covariate adaptive randomisation, a valid technique for clinical trials [19, 20] where specific participant characteristics (covariates) can be controlled for on a sequential basis based on recruitment and allocation to date [21, 22]. Randomisation will be implemented using Sealed Envelope (https://www.sealedenvelope.com), an online randomisation service. It applies a minimisation algorithm with a random component. The minimisation algorithm will balance groups on the following pre-specified covariates: gender, PTSD symptom severity (PCL-5 score) [9], and service group (military veterans vs nonmilitary service personnel vs a mix of both). PTSD symptom severity will be dichotomised into low and high categories using a fixed median split based on baseline PCL-5 scores from the initial cohort of participants enrolled prior to commencement of full randomisation (*N* = 48). This median cutoff-point will be calculated once and applied consistently to all subsequently enrolled participants and will not be updated during recruitment. For each new participant, the algorithm will calculate the marginal imbalance that would result from assignment to each group across the stratification variables. Participants will be assigned to the group that minimises overall imbalance, with a probabilistic random element (e.g. 80% allocation to the group minimising imbalance) to maintain allocation concealment and reduce predictability. The randomisation schedule will be devised prior to recruitment using an online tool and applied to eligible participants recruited online after participant identification numbers have been assigned.

### Concealment mechanism {16b}

Allocation concealment will be ensured using an automated, web-based randomisation system (Sealed Envelope, https://www.sealedenvelope.com), which implements the minimisation algorithm centrally. The randomisation sequence will be generated and applied in real time by the system and will not be accessible to the researchers involved in participant recruitment or enrolment.

Group assignment will only be revealed by the system after participants have been deemed eligible, provided informed consent, and been assigned a participant identification number. This procedure prevents the enrolling party from predicting or influencing the upcoming allocation.

## Assignment of interventions: blinding

### Who will be blinded {17a}

Due to the nature of the intervention, trial participants and those administering the intervention (e.g. angling coaches) are blinded during the intervention. As all outcome measures are anonymously self-reported, those involved in data analyses will be blind to group allocation.

Participants are not informed about which group (active vs control) they are placed in, nor are they informed of the differing survey timings between groups. Both groups eventually attend the intervention, which helps blind participants as both groups complete surveys before and after the intervention. Separate pre- and post-surveys were created and administered to each group in order to specifically tailor the wording for each group and keep them blinded. Angling coaches are blinded as they do not know if a particular participant is in the active intervention group or attending the intervention as a waitlist control group participant. All participants (eventually) take part in the angling weekend and are all treated exactly the same by the angling coaches.

### Procedure for unblinding if needed {17b}

There is no requirement for emergency unblinding procedures because the trial is waitlist controlled, and all participants eventually attend the 2-day behavioural intervention.

## Data collection and management

### Plans for assessment and collection of outcomes {18a}

All (unless otherwise requested) pre- and post-intervention data will be collected via the online platform Qualtrics. Upon request, data collected via post will be anonymously returned and manually input into a Qualtrics data file. During the intervention, participants, through the use of ID numbers and blank envelopes, anonymously self-report using pen and paper. At recruitment, participant characteristics will be collected and recorded: socio-demographics (age, gender, heritage), nature of trauma experienced, duration of PTSD, previous or current treatment/psychotropic medication prescription and use, living circumstances (alone, with a partner/friend/housemate), romantic relationship status, children, current and past employment status, income, and health service use. Postcodes will be collected for transformation into an established small area deprivation index such as the Carstairs [23]. See the “Participant timeline” section for data collection timings.

### Plans to promote participant retention and complete follow-up {18b}

All participants who fail to complete a survey are sent an email reminder 4 days after initially receiving the survey. If not completed within 2 days of this email reminder, participants are sent a text reminder to their mobile phones.

### Data management {19}

All participants are allocated a random number at recruitment using Qualtrics’s random number generator. All the following data files are password protected and securely stored. The Master File, obtained at recruitment, will be used to identify participants. The data coordinator only accesses it, while all subsequent data files are accessible to all researchers. An anonymous data file with all personal information removed is used for data analysis. A data file with personal details but no outcome data is used for communication and tracking of participants’ progress. Subsequent data files generated from pre- and post-intervention surveys contain no personal information. Paper surveys have no personal information and are stored in a secure room in a locked cabinet before input digitally.

### Confidentiality {27}

All collected information will be kept strictly confidential and will be stored in accordance with the UK Data Protection Act 1998. Personal data is collected at recruitment using Qualtrics (considered secure storage). All files containing personal information are password-protected and shared on Box.com, a password-protected file sharing platform.

### Plans for collection, laboratory evaluation, and storage of biological specimens for genetic or molecular analysis in this trial/future use {33}

N/A. No biological specimens are collected.

## Statistical methods

### Statistical methods for primary and secondary outcomes {20a}

#### Primary outcome analyses

The key analysis relates to the comparison of pre- (2 weeks before the intervention) and post-intervention measures for the intervention and control groups taken at 2 and 4 weeks after the intervention). A mixed MANOVA with one between-group factor (intervention vs. waitlist control) and repeated measures on all outcomes (baseline vs. 4-week post-intervention) will be conducted.

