### Dissemination plans {31a}

The primary outcome will be the analysis of change in PTSD symptoms pre- and post-intervention for intervention groups versus waitlist control groups. This will be disseminated in the following ways:Liaise with the Department of Health and Social Care (DHSC) to hold a workshop on NBIs for policymakers.Finalise intervention manual to ensure consistent intervention delivery going forwards.Create plain English information pamphlet to provide clear information about the intervention.A written report to the funderPapers submitted for publication in leading academic journalsPresentations at academic/health/environmental conferences and forumsDissemination events at the University of Essex and elsewhere to publicise the study findings, to distribute our plain English summary, and to develop further ties with service providers

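### The protocol states two primary questions: the 95% power belongs to a PCL-5 comparison at 4 weeks, but the primary analysis is a MANOVA on all primary outcomes

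*Protocol article*

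**What the plan says.** All references are to the protocol article.

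**PTSD as the single main outcome.** Power analysis, under Sample size {14}: "Our main dependent variable will be PTSD symptoms (as measured using the PCL-5"). The effect size is d = -0.52, described thus: "This is the effect size observed between groups at 4-week post-intervention in the developmental phase". The calculation follows: "For a 2-tailed test with 95% power, an alpha of 0.05", giving 196 in total ("98 participants in each group"). Dissemination plans {31a} agrees: "The primary outcome will be the analysis of change in PTSD symptoms pre- and post-intervention for intervention groups versus waitlist control groups".

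**Four measures as primary.** Objectives {7} words the primary objective as mean change in mental health measures and gives PTSD as an example. Outcomes {12} lists PCL-5, PHQ-9, GAD-7 and the short WEMWBS as primary, and says that mean change will be assessed for each.

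**The analysis.** Primary outcome analyses, under {20a}: "A mixed MANOVA with one between-group factor (intervention vs. waitlist control) and repeated measures on all outcomes (baseline vs. 4-week post-intervention) will be conducted".

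**Time points.** Trial design {8}: "The primary outcome will be assessed at 2-week and 4-week post-intervention and compared with the waitlist control group". Outcomes {12} and the opening sentence of Primary outcome analyses also name both 2 and 4 weeks. The model itself has baseline and 4 weeks only.

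**The concern.** A sample size calculation should describe the test that decides the trial. Here it describes a univariate comparison of one scale, while the section that fixes the primary analysis specifies a multivariate test of several. Three consequences follow.

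- The reader does not know the power of the test that will be run.
- A multivariate test rejects when any combination of the outcomes separates the arms. Rejection does not by itself show that PTSD symptoms fell, and non-rejection can occur with the planned PCL-5 effect present.
- Primary outcome analyses names no PCL-5 test and does not say which MANOVA term decides. The powered question has no designated answer.

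The time-point conflict adds a further open choice: the primary comparison is either at 4 weeks or at 2 and 4 weeks, depending on which sentence is followed.

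The trial is presented as giving definitive evidence of efficacy in people with PTSD and is meant to inform policy, so it matters which hypothesis the headline result addresses.

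**Working it through.** **Inputs from the protocol:** d = 0.52 in absolute value, between groups at 4 weeks; two-sided alpha 0.05; power 95%; 98 per arm; 1:1 allocation; four primary measures.

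**Assumptions not in the protocol:** the pre-post correlation rho, the correlation r between the outcomes' change scores, and the effects on PHQ-9, GAD-7 and WEMWBS. Equal variances and equal baseline means are assumed, and signs are aligned so that positive means improvement.

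**1. Reproduce the stated N.** Two-sample t-test with noncentrality d·sqrt(n/2):
- n = 97 per arm: power 94.98%.
- n = 98 per arm: power 95.2%.

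So 98 per arm is exactly the univariate independent-samples calculation for PCL-5.

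**2. Power of the four-outcome MANOVA at the same n.** With two time points, testing group by time on four outcomes is Hotelling's T² on four change scores: F with 4 and 191 degrees of freedom, noncentrality (n/2)·D² = 49·D², where D is the Mahalanobis distance between the arms. Taking this term as the deciding one is my reading, since the protocol names none.

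The stated d is on post-scores. On the change scale it becomes d_c = 0.52 / sqrt(2(1 − rho)), which equals 0.52 only if rho = 0.5.

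*Case A: the other three outcomes add no separation beyond PCL-5, so D² = d_c².* This is the lowest power possible for a given PCL-5 effect.

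| rho | d_c | 49·D² | Power |
|---|---|---|---|
| 0.3 | 0.439 | 9.46 | 67.6% |
| 0.5 | 0.520 | 13.25 | 83.5% |
| 0.7 | 0.671 | 22.08 | 97.5% |

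At rho = 0.5, this case needs 140 per arm (280 analysed) for 95%.

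*Case B: all four outcomes have d = 0.52 and rho = 0.5.* D² = 4 × 0.2704 / (1 + 3r).
- r = 0.4: D² = 0.492, noncentrality 24.1, power about 98%.
- r = 0.8: D² = 0.318, noncentrality 15.6, power about 90%.

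**3. Can the MANOVA reject without a PTSD effect?** Set the PCL-5 effect to zero and give the other three outcomes d = 0.4 on the change scale. At 98 per arm the test rejects in 93%, 95% and 99% of trials for r = 0.3, 0.5 and 0.7. These are illustrations of what rejection can mean, not forecasts.

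**4. Power of a single PCL-5 test.** Adjusting the 4-week score for baseline gives an effective d of 0.52 / sqrt(1 − rho²). At 98 per arm, power is 96.7%, 98.7% and 99.9% for rho = 0.3, 0.5 and 0.7. The development-phase attrition of about 25% leaves 264 × 0.75 = 198 analysed, just above 196.

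**The case against.** The best defence is that the MANOVA does match a primary question in the protocol. Objectives {7} and Outcomes {12} treat all four measures as primary, and a four-outcome test fits that set. This stands. A reader might infer that the trial tests something other than its own primary question, but the documents do not support so strong a statement: they hold two primary questions, and the calculation and the analysis each serve a different one.

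Other tempting readings also go too far:

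- *The trial is underpowered.* Not shown. MANOVA power lies below or above 95% depending on correlations that the protocol does not give. The 83% figure alone would mislead, because it holds only at a pre-post correlation of 0.5.
- *The 2-week data are never analysed.* Not so. Secondary analyses uses 2-week PCL-5 scores for clinically significant and reliable change. They are absent only from the specified primary model.
- *No effect on PCL-5 will be reported.* Outcomes {12} promises mean change for each measure. What is missing is a rule for which result decides.
- *The false-positive rate is inflated by separate tests.* The protocol does not state that four unadjusted tests will be run, and the order and adjustment of follow-up tests may properly sit in the analysis plan that {20c} defers to.

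That deferral does not remove the core point. The protocol itself fixes the MANOVA as primary and attaches a power figure belonging to another test.

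**Conclusion.** The concern holds as an internal inconsistency over what the primary question is. That 95% is the power of a two-sample PCL-5 test is certain, because the stated N reproduces exactly. The size of the discrepancy is not certain: across the cases examined, MANOVA power runs from about 68% to about 98%, all of it resting on assumed correlations and, in the all-four case, on assumed effects for the other measures. That rejection cannot be attributed to PTSD follows from the nature of the test and needs none of these figures. The conflict over the 2-week point is plain from two consecutive sentences in Primary outcome analyses. Followed exactly, the plan leaves its headline test unable to answer the PTSD question on which the trial was sized, so this should be corrected before the final analysis.

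**What to change.** Reconcile Objectives {7}, Trial design {8}, Outcomes {12}, Power analysis {14}, Primary outcome analyses {20a} and Dissemination plans {31a}.

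**Preferred:** name PCL-5 at 4 weeks as the single primary endpoint, as Power analysis already treats it. Test it in one baseline-adjusted repeated-measures model that includes week 2, and report the adjusted mean difference at 4 weeks with its 95% CI. The planned 98 per arm then gives at least the stated power. Make PHQ-9, GAD-7 and short WEMWBS secondary, and keep the MANOVA as supportive only.

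**Alternative:** keep four primaries, state the deciding test and a multiplicity rule, settle the time points, and restate the power for that analysis with its assumed correlations.

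The preferred route needs no new data and no change to recruitment. Its cost is amended wording and the relabelling of three measures from primary to secondary. The alternative keeps the labels but needs a new power calculation, which may ask for more participants.
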